## Abstract

**Background:**

Interventions to improve the nutritional status of older adults and the integration of formal and family care systems are critical research areas to improve the independence and health of aging communities and are particularly relevant in the rehabilitation setting.

**Objective:**

The primary outcome aimed to determine if the FREER (Family in Rehabilitation: EmpowERing Carers for improved malnutrition outcomes) intervention in malnourished older adults during and postrehabilitation improve nutritional status, physical function, quality of life, service satisfaction, and hospital and aged care admission rates up to 3 months postdischarge, compared with usual care. Secondary outcomes evaluated include family carer burden, carer services satisfaction, and patient and carer experiences. This pilot study will also assess feasibility and intervention fidelity to inform a larger randomized controlled trial.

**Methods:**

This protocol is for a mixed-methods two-arm historically-controlled prospective pilot study intervention. The historical control group has 30 participants, and the pilot intervention group aims to recruit 30 patient-carer pairs. The FREER intervention delivers nutrition counseling during rehabilitation, 3 months of postdischarge telehealth follow-up, and provides supportive resources using a novel model of patient-centered and carer-centered nutrition care. The primary outcome is nutritional status measured by the Scored Patient-Generated Subjective Global Assessment Score. Qualitative outcomes such as experiences and perceptions of value will be measured using semistructured interviews followed by thematic analysis. The process evaluation addresses intervention fidelity and feasibility.

**Results:**

Recruitment commenced on July 4, 2018, and is ongoing with eight patient-carer pairs recruited at the time of manuscript submission.

**Conclusions:**

This research will inform a larger randomized controlled trial, with potential for translation to health service policies and new models of dietetic care to support the optimization of nutritional status across a continuum of nutrition care from rehabilitation to home.

**Trial Registration:**

Australian New Zealand Clinical Trials Registry Number (ACTRN) 12618000338268; https://www.anzctr.org.au/Trial/Registration/TrialReview.aspx?id=374608&isReview=true (Archived by WebCite at http://www.webcitation.org/74gtZplU2).

**International Registered Report Identifier (IRRID):**

DERR1-10.2196/12647

## Introduction

### Background

In older Australians, protein-energy malnutrition (PEM) is highly prevalent and a strong independent contributor to poor health, but is preventable and treatable [1-4]. PEM is defined as the unintentional and preventable loss of lean tissues such as muscle, blood and immune cells, and viscera, with or without fat loss, due to prolonged inadequate dietary intake or uptake of protein and energy [1]. Although PEM may occur at any age, it is most prevalent in older adults due to the higher prevalence of PEM risk factors such as multimorbidity and polypharmacy, and the physiological and social changes that occur during the aging process [5]. A sufficient increase in protein and energy intake and uptake to meet individualized requirements will cease the loss of lean tissues and reverse PEM, except in severe cachectic states [1]. However, encouraging malnourished older adults to consume appropriate types and quantities of foods encounters many diverse barriers due to its deeply complex physiological, socio-economic, and environmental risk factors, as well as unique presentation in each individual [5,6]. Individualized and long-term nutrition support is required to overcome these barriers and enable the older adult to improve their nutritional status [3,7]. Thus, the model of care adopted by many hospitals, which involves short-term treatment by health professionals during a health care admission only, is usually insufficient to effectively treat PEM [5,8].

Interventions to improve the nutritional status of older adults and the integration of formal and family care systems are critical research areas of the United Nations (items 2.6.10 and 2.10.7) [9], and implementing these approaches in rehabilitation facilities is of primary importance in Australia. Australian rehabilitation units have the highest prevalence of PEM internationally (45%-65% versus 30%-45% in the United States, Europe, and Asia when using the same diagnostic tool, N=17 studies, N=4591 participants) [10]. Although the goal of rehabilitation is to increase independence, observational research identified that older patients admitted to rehabilitation with PEM and receiving usual care were being discharged to the community with PEM, where they remained malnourished for at least 12 weeks in their own homes [10]. A recent meta-analysis found the prevalence of PEM in older Australians living in their own homes is 6% (95% CI, 4.4%-8.2%), which represents 228,000 malnourished older adults in 2017 [11]. Further downstream health consequences are severe, where PEM significantly predicts decreased physical function, institutionalization, and rehospitalization, poor quality of life, and death [3,10,12].

Family carers are an untapped resource and feasible group of people eager to support malnourished patients in the long-term [13]. There is a direct causal link between poor nutrition knowledge of family carers and increased PEM risk in older adults [14]. Conversely, studies have found that empowering family carers of malnourished older adults living at home (via training, education, and follow-up) can improve the nutritional status, quality of life, and physical function of the older adult, without increasing carer burden [15,16]. A qualitative study found that family carers believe it is the responsibility of rehabilitation staff to ensure the family carers are engaged as key members of the nutrition care team and that their preexisting caring relationship with the older adult is recognized and respected [13]. The qualitative study further identified the preferred method of engagement was via telephone, which is supported by a recent systematic review and meta-analysis, which found that telehealth was a feasible and effective method to provide PEM treatment post-hospital discharge [17]. The FREER (Family in Rehabilitation: EmpowERing Carers for improved malnutrition outcomes) pilot study will be the first to translate this evidence as a patient- and carer-centered model of care for the rehabilitation and post-rehabilitation older adult setting.

Therefore, this study aims to (1) determine if the FREER intervention in malnourished older adults during and postrehabilitation improves nutritional status, physical function, quality of life, service satisfaction, and hospital and aged care admission rates up to 3-months post discharge, compared with usual care, (2) evaluate secondary outcomes including carer burden, carer service satisfaction, and patient and carer experiences, and (3) assess the feasibility and intervention fidelity to inform a larger randomized controlled trial (RCT).

## Methods

### Study Design

This is the protocol for a pragmatic mixed-methods two-arm historically-controlled prospective pilot intervention study. This protocol has been reported according to the Standard Protocol Items: Recommendations for Intervention Trials (SPIRIT) 2013 Checklist [18] as well as the Template for Intervention Description and Replication (TIDieR) Checklist [19]. The FREER pilot study has been prospectively registered with the Australian New Zealand Clinical Trials Registry Number (ACTRN12618000338268).

### Historical Control Group and Usual Care

Participants in a prospective observational study conducted 2013-2014 will act as a historical control group [10]. The historical control participants were recruited from 2 government-funded rural rehabilitation units in New South Wales (n=14 and n=16 participants respectively), one of which is the study site for the FREER pilot study, with participants having the same eligibility criteria as FREER. They had a mean age of 80 years and 57% were female [10]. The historical control group received usual care, which included being placed on a standard high protein-high energy diet [20] during admission and receiving standard nutrition support from the existing rehabilitation dietitian, but only if referred by the usual clinical pathways. The usual care provided to the historical control group has not changed at the time of the FREER pilot study and therefore is the same care provided to patients’ ineligible for FREER. Although the service was available, no participants in the historical control group received outpatient follow-up by a community dietitian [10]. Family carers of patients in the control group were not engaged specifically but may have been involved in some discussions with the rehabilitation dietitian during their care recipient’s admission. The outcomes in the historical control group have been published elsewhere [10,12].

Inclusion and exclusion criteria.InclusionAdults (≥65 years) admitted to rehabilitation with protein-energy malnutrition diagnosed by the Patient Generated Subjective Global AssessmentHaving a family carer (≥18 years). Family carers will be considered persons (including family or friends) who assist with activities of daily living up until the point of hospital admission, with no financial reimbursement for caring duties beyond a carers pension, with contact with the patient of ≥4 times per week, either in person or by telephoneFamily carer is English speaking and able to act as translator for the patient if the patient is non-English speakingFamily carers do not have any health-related eligibility criteria applied; however, need to have sufficient independence to assist the patients with activities of daily livingExclusionPatient and/or carer are unable to give consentPatient is receiving enteral or parenteral feedingDischarge is planned in <6 days from date of eligibility screeningPatients living in residential aged care prior to rehabilitation admission are excluded. However, patients previously community-dwelling but discharged to residential aged care will be included using an intention-to-treat approachThe patient and/or carer do not live in the local area. For example, admitted during holiday, or plan to move away from the local area (1.5 hours drive from the unit) within 3 months postdischarge

### Sample Size

As a pilot intervention study, the sample size was chosen to reflect resources and funding availability, as well as aiming to match control and intervention participants in a 1:1 ratio. Therefore, the current pilot intervention will aim to match the historical control group sample size (n=30), for a final sample of n=60 patients. The historical control group did not collect data on family carers, as they were not engaged as part of usual care, and therefore not available for recruitment. Therefore, the sample size for family carers will be n=30.

### Blinding and Randomization

Randomization is not possible due to the study design. The use of a historical control group for the pilot study was chosen to limit intervention contamination within the small rehabilitation unit as resources did not allow for 2 prospective cluster sites to be recruited. Blinding of participants and personnel to the intervention is not possible due to the nature of the intervention (nutrition counseling), study design of the historical control group (researchers not blinded in the historical control group), and lack of resources to fund blinded outcome assessments for the pilot intervention study.

### The FREER Intervention

By integrating formal and family care for malnourished rehabilitation patients, the FREER intervention aims to establish family carers as partners in the nutrition care team, thereby empowering and enabling them to manage and improve the efficacy of their preexisting nutrition-related care in the long term. In order to truly empower the family carer, the level of engagement between the dietitian, family carer, and patient in the FREER intervention model of care is derived from the Patterson, Kirk, and Wallace model, in which all team members have equal involvement and influence [21].

We have applied the four-step systematic approach for using the theoretical domains framework [22] to develop and establish the preliminary feasibility of the FREER intervention strategies. This was done through literature reviews [15-17], a qualitative study of family carer support needs and preferences [13], and stakeholder engagement (n=20 health care staff, unpublished). This pilot study will now establish preliminary efficacy and feasibility of the FREER intervention. All FREER intervention components will be delivered by the study dietitian and will use 3 individualized and needs-based strategies described in Multimedia Appendix I [23,24].

### Psychological Model of Behavior Change

Patient and family carer engagement strategies will apply the theory of planned behavior and reasoned action to increase an individual’s ability to make recommended changes [25]. Therefore, all engagements with the study dietitian will include education and shared goal setting, problem-solving, and contingency planning [25]. This model of behavior change was selected by the research team as it was considered the most appropriate to create partnerships with the patient and family carer, to lead to empowerment rather than dependency.

### Quantitative Outcome Measures

The selected quantitative outcome measures have been validated and previously piloted in the target population [10,12], and are outlined in Table 1. Nutritional status as defined by the PG-SGA numerical score [26] is the primary outcome (increasing score indicates increasing severity of PEM with typical scores 0-30). The PG-SGA was chosen in preference to the Mini Nutritional Assessment [27] and other nutrition assessment tools as both its score and categorization have the strongest criterion validity in this population and it has shown sensitivity to change in 1 week [1]. Secondary outcomes for the patient include (1) additional measures of nutritional status (PG-SGA rating of A, B or C), (2) energy and protein intake (kJ and grams per day), (3) mid-arm circumference (MAC), (4) physical function by Modified Barthel Index (MBI) [28], (5) Functional Independence Measure (FIM) [29], (6) body weight (kg), (7) health-related quality of life using a generic preference-based instrument (AQoL-6D) [30], (8) rehabilitation length of stay, (9) patient nutrition service satisfaction as per purpose developed Nutrition Service Satisfaction Survey modified from the Patient Satisfaction Survey with Inpatient Clinical Nutrition Services (Multimedia Appendix 2) [31], (10) 3 month rehospitalization (yes or no; and length of stay), (11) aged care admission (yes or no; and level of care). Secondary outcomes of the family carer are carer burden (Zarit Burden Interview Score [32]) and carer nutrition service satisfaction (Carer Nutrition Service Satisfaction Survey modified from the Patient Satisfaction Survey with Inpatient Clinical Nutrition Services and shown in Multimedia Appendix II) [31]. All assessment tools and physical measures for the patient will be completed by the study dietitian during patient interview, excepting the service satisfaction questionnaire which will be completed by the patient. All assessment tools for the family carer will be self-completed unless via telephone interview, or the carer has limitations with reading or writing.

The primary and secondary outcomes will be measured at baseline (recruitment T1), rehabilitation discharge (T2), and 12-weeks postdischarge (T3), as described in Table 1. Outcomes will be assessed at the rehabilitation site (T1 and T2) and a home visit or medical records as relevant (T3). If the participant is not able to be assessed at discharge at the rehabilitation site, T2 outcomes will be informed via telephone interview and medical records wherever possible; however, the physical measures including a component of the PG-SGA and the MAC would not be performed in this instance.

**Table 1 table1:** FREER pilot study primary and secondary outcomes, assessment methods, and timepoints.

Outcome	Baseline (T1)	Discharge (T2)	Postdischarge (T3)	Measure and source of data
Nutritional status	X	X^a^	X	PG-SGA^b^ score and category Patient and carer interview
Weight (kg)	X	X	X	Calibrated study scales or medical records Patient interview
Energy intake (kJ)	X	X	X	24hr dietary recall Patient and carer interview
Protein intake (g)	X	X	X	24hr dietary recall Patient and carer interview
Mid-arm circumference	X	X	X	Tape measure Patient interview
Physical function	X	X	X	Modified Barthel Index Patient and carer interview supported by allied health care team Medical records
Physical function	X			Functional Independence Measure Medical records
Health-related quality of life	X	X^a^	X	AqoL-6D^c^ Patient interview
Patient nutrition satisfaction			X	Patient Satisfaction Survey Self or carer-completed
Rehabilitation length of stay		X		Medical records
Rehospitalization and length of stay			X	Medical records
Residential aged care admission			X	Medical records Patient or carer report
Carer burden		X	X	Zarit Burden Interview Self-completed
Carer nutrition satisfaction			X	Carer Satisfaction Survey Self-completed
Patient and carer experiences and perceptions of value^d^			X^e^	Qualitative interview conducted via telephone

^a^If T1 and T2 occur 6 days or less apart this measure will not be repeated as it will have assumed not to have significantly changed within that short time period as per feasibility data [10].

^b^PG-SGA: Patient Generated Subjective Global Assessment.

^c^AQoL-6D: Assessment of Quality of Life-6D.

^d^A subgroup of participants will be invited to participate by consecutive sampling with a target sample size of n=10 carers and n=10 patients.

^e^The interviews will be conducted up to 2 weeks following T3 by an independent researcher.

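### Two rules for the discharge visit (T2) leave some values of the primary outcome, the PG-SGA score, either not comparable with the other visits or merely assumed

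*Protocol article*

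**What the plan says.** All references are to the Protocol article.

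- **Outcome and visits (Quantitative Outcome Measures).** The primary outcome is the numerical PG-SGA score. Higher is worse, and typical values run from 0 to 30. It is due at recruitment (T1), rehabilitation discharge (T2) and 12 weeks after discharge (T3). The A/B/C rating from the same tool is a secondary outcome.
- **Telephone rule (same section).** If a patient cannot be assessed on site at discharge, "T2 outcomes will be informed via telephone interview and medical records wherever possible", but "the physical measures including a component of the PG-SGA and the MAC would not be performed in this instance". The text does not say how the incomplete PG-SGA is then totalled or rated.
- **Six-day rule (Table 1, footnote a).** For the PG-SGA and the AQoL-6D: "If T1 and T2 occur 6 days or less apart this measure will not be repeated". The reason given is an assumption of no significant change, citing reference 10 as feasibility data. Historical Control Group and Usual Care identifies reference 10 as the observational study that supplies the controls. The T2 entries for weight, intake, mid-arm circumference and Modified Barthel Index carry no such footnote.
- **Reason for choosing the tool (Quantitative Outcome Measures).** Among others, "it has shown sensitivity to change in 1 week".
- **Analysis (Statistical Analysis).** Change over time within the intervention arm uses linear mixed models. The group comparison uses generalized estimating equations (GEE) with group and time as main predictors, adjusted for the baseline value.

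**The concern.** Both rules act on the primary outcome at one of only two post-baseline visits.

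A PG-SGA obtained without its physical component is a different measurement from the full score at T1 and T3. Because higher is worse, leaving out a part that can only add points moves the total toward better nutrition, so a telephone assessment could look like improvement. The A/B/C rating would likewise be made without the physical findings.

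The six-day rule tells staff not to take the primary outcome because it is assumed unchanged. That assumption comes from patients on usual care and is applied to an intervention meant to change the score. If the T1 value then serves as T2, early change is hidden. Footnote a is also a data-collection rule: a later analysis plan can decide how to treat the gap but cannot recover a score that was never taken.

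**Working it through.** The document gives no sample-size, power or precision figure that depends on these rules, so there is nothing of its own to reproduce. What follows is illustrative arithmetic, then a comparison of the passages.

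**Inputs from the document.** 30 patients per arm (Sample Size); higher score is worse; two post-baseline visits; average stay 22 days (Participants and Setting).

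**Assumed inputs, not in the document.** The physical component contributes points to the numerical score; *k* patients per arm are affected; *c* points are lost per telephone assessment; *d* is the true T1–T2 change in a patient whose T1 value stands in for T2.

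**A. Telephone total with the missing component counted as zero.** Shift in one arm's T2 mean = −(*k*/30) × *c*.

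| *k* of 30 | *c* = 1 | *c* = 2 | *c* = 3 |
|---|---|---|---|
| 3 (10%) | −0.1 | −0.2 | −0.3 |
| 6 (20%) | −0.2 | −0.4 | −0.6 |
| 9 (30%) | −0.3 | −0.6 | −0.9 |

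The range is 0.1 to 0.9 points toward apparent improvement. If T2 and T3 are averaged with equal weight, it halves to 0.05 to 0.45.

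**B. T1 used as T2.** The arm's mean T1–T2 change is pulled toward zero by (*k*/30) × *d*. With *k* = 1 and *d* = 1 this is 1/30 = 0.03. With *k* = 6 and *d* = 3 it is 0.2 × 3 = 0.6. Averaged over T2 and T3, the range is 0.02 to 0.3.

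**C. What reaches the group comparison.** Under A, the error in the T2 contrast (intervention minus control) is −(share × points lost in intervention) + (share × points lost in control). It cancels if the two products are equal, and equals the full figure in A if only the intervention arm is affected. The document does not say which T2 rules the controls followed, so neither case can be asserted. The within-arm analysis of change over time has no such cancellation.

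**D. The six-day rule beside the rest of the text.**
- The tool is credited with detecting change in 1 week, while no change is assumed for intervals up to 6 days. These intervals are close but not the same.
- Intake by 24-hour recall and mid-arm circumference by tape are still scheduled at T2 and need the patient. In such cases the plan takes secondary measures at discharge and omits the primary one.
- Planned early discharge is excluded and the average stay is 22 days, so short T1–T2 intervals are probably uncommon. They can still arise when discharge comes earlier than planned or when recruitment follows screening by some days.

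**The case against.** The strongest reply is that the article states neither error. It does not say that a partial total is calculated and analysed, nor that T1 is entered in the T2 field. Scoring of incomplete instruments is commonly left to an analysis plan, which is not shown. This stands to the extent that a reader who infers that wrong values are put into the primary outcome goes beyond the text. It does not dispose of the point: the text has T2 outcomes informed by telephone while part of the primary measure is missing, and it directs that the PG-SGA not be repeated because no change is assumed. Followed as written, the rules yield a non-comparable or an assumed value.

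Other stronger readings also fail:

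- **A contradiction between 6 days and 1 week.** Sensitivity at 7 days does not refute stability at 6 or fewer. It is a tension, made sharper by the usual-care source of the assumption.
- **A mismatch with the exclusion criterion.** The exclusion applies when discharge "is planned in <6 days from date of eligibility" screening, so it concerns planned discharge counted from screening. Footnote a concerns the actual interval from T1 to T2. The clocks differ, and the two limits need not agree.
- **Understated variance at T2.** A T1 value used at T2 keeps the between-patient spread of T1. Only the spread of the T1–T2 change would shrink.
- **Bias between the groups.** This is possible but not shown. Since footnote a relies on the control study, similar handling there is also possible.

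It is also fair that omitting two instruments over a short interval may be meant to spare patients, and that this is a pilot sized by resources.

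**Conclusion.** The point holds in a limited form. Some T2 values of the primary outcome will be non-comparable (telephone) or assumed (short interval), and the article does not rule out analysing them as ordinary scores. T1 and T3 are not affected by either rule.

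The size is unknown. The 0.1–0.9 point shift in one arm's T2 mean rests wholly on assumed telephone use of 10–30%, an assumed loss of 1–3 points, and counting the missing part as zero. The document gives no standard deviation or target effect against which to judge it. The two errors can work in opposite directions: the first lowers the score, and the second hides change of either sign. The matter deserves correction because it concerns the primary outcome and the remedy is cheap; it does not undermine the T3 comparison.

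**What to change.** 1. Remove footnote a from the PG-SGA entry and score the PG-SGA at the T2 contact whenever that takes place. Do not enter T1 as an observed T2 value. For patients already assessed under the present rule, record T2 as missing.
2. Do not analyse a telephone PG-SGA as a full score or as an A/B/C category. Treat the T2 total and category as missing in the main model, and keep the items that were collected.
3. Add a sensitivity analysis using the total without the physical component at all visits in both groups. This needs component-level scores to be retained.
4. Apply the same rules to the historical controls as far as their data allow, and state where they do not.
5. Report the number of missing T2 scores and the reasons, by group.

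**Cost.** Mostly wording, one added assessment for patients with a short interval, and slightly fewer T2 totals. Setting values to missing is not free of bias: unweighted GEE assumes that missingness is completely at random or explained by the covariates, and discharge without an on-site assessment may depend on the patient's condition. Hence item 5; a likelihood-based mixed model could also serve as a check.
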